#### Cell damage

Recent studies demonstrated a protective effect of short term fasting on healthy peripheral blood cells during chemotherapy (14). Thus, we aim to assess DNA damage in peripheral blood mononuclear cells (PBMCs) using the level of y-H2AX intensity after the administered chemotherapy (in case of more than one chemotherapy, the blood will be drawn right after the first chemotherapy). Blood will be drawn at the first day of CHT, six weeks and 12 weeks after the start of the CHT. As the cell damage is dependent on the day CHT is given, time points will be adjusted +/- 1 week depending on the days CHT is administered (e.g. in case of delayed CHT or public holidays). Blood samples will be stored in X-VIVO-medium with 10% DMSO (1 x 10^7^ cells/mL) at -80°C.

When DNA is damaged, the histone H2AX gets phosphorylated at Ser139 in the area of damage. For detection of phosphorylated H2AX (γH2AX), PBMCs, isolated as described above, will be cytocentrifuged onto glass slides (2 x 10^4^ cells/slide), fixed by paraformaldehyde, treated with 0.1% Triton X100 and stained immunocytologically by using a specific Flour 488 labeled antibody (Abcam). A counterstain will be performed by DAPI and the slides will be evaluated by laser scanning microscopy. For detection of γH2AX in tumor tissue, formalin fixed and paraffin embedded tumor tissue will be immunohistochemically stained by using an anti-γH2AX (Ser 139) antibody (Cell Signaling). The staining will be performed with EnVision™ staining kit (Dako) according to the manufacturer’s instructions. The evaluation will be performed by light microscopy.

#### Long-term effects

Long-term effects after termination of the intervention on fatigue, QoL, laboratory changes and rate of voluntary continuation of IF will be assessed in a single follow-up visit at 6 months (+/- 2 weeks) after completion of CHT. If tumor status is obtained through routine clinical follow-up, it will be assessed through imaging (when appropriate) and biomarker response.

### Methods against bias

#### Selection bias

Potential trial eligibility will be assessed during an interdisciplinary tumor conference and all patients will be approached consecutively for trial participation. Final eligibility will be determined during the consultation for obtaining informed consent for the planned CHT. For all eligible non-participants, the reason for non-participation will be documented. Moreover, eligible participants and non-participants will be compared regarding age, cancer type, ECOG and FIGO stage to identify potential selection processes.

#### Detection bias

All outcomes will be predefined, and the majority of outcome parameters are assessed by clear definitions that do not leave much room for interpretation. Subjective outcomes are documented by the participants themselves and cannot be influenced by the study staff.

### Statistical analysis

Patients will be randomized to the intervention or control group (1:1) stratified by tumor entity and study site. The primary endpoint, the difference of the mean change of fatigue over a period of three months as measured by the FACIT-FS© score, will be compared between both groups using mixed models. Confounders such as age, type of CHT, neoadjuvant/adjuvant vs metastatic treatment, the Eastern Cooperative Oncology Group performance status (ECOG), histological tumor grade, and Fédération Internationale de gynécologie et d’Obstetrique (FIGO) -stage will be included in the mixed models. Laboratory data, as well as QoL questionnaire-based outcomes will also be assessed using mixed models. Missing data for the primary outcome as well as secondary outcomes with the potential to become main outcomes in subsequent larger trials will be imputed. Where possible, missing questions from FACT^©^ questionnaires will be prorated using the average of the other answers in the subscale (prorated subscale score = [sum of the item scores]*[N of items in subscale]/[N of items answered]) as long as more than 50% of the items are answered. Data will be imputed by drawing values from the distribution of the control group (jump to reference).

A comprehensive summary will be given for primary and secondary endpoints, including absolute and relative frequencies for categorical and binary variables as well as mean and standard deviation or median and interquartile range and minimum-maximum for all data with at least interval scale level. Pathological response rates after neoadjuvant CHT will be compared using the Chi square test. Radiological response rates (complete response, partial response, stable disease, and progressive disease) will be compared between the arms at 3 months and 6 months using the Mann-Whitney-U-tests. The occurrence of any adverse event as well as the occurrence of grade 3 or higher adverse events will be compared between both groups using the Chi square test. And a list of immunological and metabolic parameters will be compared between both groups using the Mann-Whitney-U test. A paired Wilcoxon test will be used to compare the change in BMI over three months between both groups.

Analyses will be performed as (1) modified intention-to-treat (ITT) population including all patients randomized who have at least received the first chemotherapy cycle. Patients will be analyzed in the group they were randomized to; (2) per-protocol (PP) sets, including all patients who have at least completed one/two/three or all chemotherapy cycles without major protocol violations. Safety will only be assessed in the per-protocol subset. Subgroup analyses will be performed by tumor type and type of CHT regime for groups with an adequately high number of participants. Furthermore, the parameters will be displayed graphically, and appropriate descriptive statistics will be employed. The significance level will be bilaterally set at 5%. 95% confidence intervals will be reported where appropriate. Due to the exploratory nature of secondary outcomes, no adjustments will be made for multiple testing.

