### Recruitment and randomization

Patients will be recruited at the time of diagnosis and discussion of the treatment plan after the interdisciplinary tumor conferences of each hospital had finalized the treatment schedule. Written informed consent will be obtained from all participants prior to randomization and baseline visit. Patients can withdraw consent and effectively withdraw their trial participation at any point without any disadvantages. A screening checklist including all inclusion and exclusion criteria will be assessed by a medical doctor prior to randomization. Variable block randomization stratified by tumor entities and study site will be used to randomly assign participants to intervention or control group (1:1). Block length will be disclosed upon completion of the trial. The preparation of the randomization lists will be performed by a statistically trained researcher not involved in the recruitment, allocation, or assessment of the participants. Randomization lists will be uploaded in RedCap and cannot be viewed or changed during the trial. Group allocation will be performed over the RedCap database. Patients will be allocated after obtaining consent and completing baseline assessments to confirm eligibility.

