### Eligibility criteria

Adult female patients with histologically confirmed gynecological cancers (ovarian, breast, cervical or uterine) are eligible to participate in this study. Potential trial participants will be identified through interdisciplinary tumor conferences at both study centers and potential study participation will be documented in the protocol. A complete list of inclusion and exclusion criteria can be found in **Table 2**. Exclusion criteria were chosen to minimize the risk for critically ill patients as well as to exclude diseases significantly impacting the normal metabolism.

**Table 2 T2:** Inclusion and exclusion criteria of the study.

Inclusion criteria	
	◼ Women with histologically confirmed ovarian (including peritoneal cancer or cancer of the fallopian tubes), breast, endometrial or cervical cancer ◼ ≥ 18 years of age
	◼ BMI ≥ 19 kg/m^2^ ◼ ECOG 0-2 at baseline ◼ Anticipated life expectancy of > 6 months ◼ Planned to receive intravenous chemotherapy for at least three months ◼ Planned to receive chemotherapy including at least one topoisomerase inhibitor or alkylating agent
	◼ Ability to understand nature and effects of the trial participation
Exclusion criteria	
	◼ Simultaneous radiation therapy ◼ Received Chemotherapy in the last six months ◼ Weight loss of >10% in the last three months ◼ Type I diabetes or intensified insulin treatment
	◼ Kidney failure (creatinine above 2mg/dl), liver failure (liver enzymes above 2,5x the upper limit of normal)
	◼ Current or past eating disorders ◼ Other psychiatric diseases
	◼ Myocardial infarction, stroke or pulmonary embolism within the last 3 months
	◼ Unstable heart disease ◼ Severe internal co-morbidities
	◼ Enterostomy, short bowl syndrome
	◼ Pregnancy & breastfeeding period
	◼ Participation in another interventional trial likely to interfere with the study outcome ◼ Language difficulties

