### Outcome measures

#### Primary outcome

Primary outcome of this study is the difference of the mean change in fatigue from baseline to last follow-up time point of the active trial period (3 months) between the IF group and the control group. A variation of up to ± 1 week for trial termination is allowed due to potential delays of CHT (e.g. due to insufficient blood values or public holidays).

Fatigue is measured after each chemotherapy treatment using the Functional Assessment of Chronic Illness Therapy-Fatigue Scale (FACIT- FS©). This questionnaire assesses cancer therapy related fatigue. It is part of the FACIT-F© questionnaire (22) which is a combination of the Functional Assessment of Cancer Therapy general core questionnaire (FACT-G©) and the FACIT-FS©. The FACIT-FS© includes 13 fatigue related questions, which are rated on a 5-point Likert scale (not at all to very much) over the last 7 days. Scores will be calculated according to published scoring algorithms.

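### The primary mixed model names FIGO stage as a term, but eligible breast cancer patients have no FIGO stage and no rule says how they stay in the analysis

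*Protocol article*

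**What the plan says.** The primary endpoint is "the difference of the mean change in fatigue from baseline to last follow-up time point of the active trial period (3 months", compared between the arms with mixed models (Primary outcome; Statistical analysis). The covariates are introduced as "Confounders such as age, type of CHT, neoadjuvant/adjuvant vs metastatic treatment, the Eastern Cooperative Oncology Group performance status (ECOG), histological tumor grade", and the sentence closes with "FIGO) -stage will be included in the mixed models".

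The Eligibility criteria section admits "Adult female patients with histologically confirmed gynecological cancers (ovarian, breast, cervical or uterine) are eligible to participate in this study". Breast patients are clearly expected: FACT-B is a planned questionnaire, CA 15-3 is a listed tumour marker, and the sample size rests on a study in breast and ovarian cancer.

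On allocation, the Statistical analysis section states "Patients will be randomized to the intervention or control group (1:1) stratified by tumor entity and study site". Neither stratification factor is among the named covariates, and nor is baseline FACIT-FS.

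On missing data, the article says "Missing data for the primary outcome as well as secondary outcomes with the potential to become main outcomes in subsequent larger trials will be imputed". It also gives a prorating rule for questionnaire items. Missing covariates are not mentioned.

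The analysis set is a modified intention-to-treat population: everyone randomised who received at least the first chemotherapy cycle.

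**The concern.** FIGO staging applies to cancers of the gynaecological organs. The article counts breast cancer among gynaecological cancers, which is probably how the term came to be applied to all patients. The Selection bias section does the same when it compares participants with non-participants on FIGO stage.

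For a breast patient, a named term of the primary model is therefore undefined. If the field is left empty and the software deletes incomplete records, as is the usual default, the patient leaves the analysis although her fatigue scores are complete. Imputing outcomes does not bring her back, because it is the covariate that is missing. Two things are at stake: the primary result could describe a population other than the stated one, and power could be well below plan. How the field is coded would also be an undocumented choice in an open-label trial, possibly made after outcomes are known.

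**Working it through.** **Inputs from the Sample size section.** Difference 9.1 points, SD 13.7, two-sided alpha 0.05, power 90%, 48 per arm, raised to 55 for drop-out.

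**Inputs not in the article (assumed).** The share of breast patients, and the correlation rho between baseline and 3-month FACIT-FS.

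**1. The plan's own figure.** n per arm = 2 × (1.960 + 1.282)² × 13.7² / 9.1² = 2 × 10.51 × 2.266 = 47.6, so 48. The exact t calculation gives 48.6, so 49. Power at 48 is 90.2% (normal) or 89.6% (t). The stated sample size reproduces and is not in dispute.

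**2. What default fitting does.** A mixed model was fitted to simulated data on 96 patients with four time points each; 45 had breast cancer and no FIGO value.
- Complete-case fitting kept 51 patients (204 of 384 rows) and lost all 45 breast patients.
- With FIGO as a categorical term that had a 'not applicable' level, all 96 patients (384 rows) stayed in.

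The loss is real under the default, and it depends entirely on coding.

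**3. Power if breast patients are deleted.** Because randomisation is stratified by tumour entity, the loss is roughly equal in both arms. With breast share s, m = n × (1 − s) per arm, and power = Φ(9.1 / (13.7 × √(2/m)) − 1.960).

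| Assumed breast share | m from 48 | Power | m from 55, no other loss | Power |
|---|---|---|---|---|
| 30% | 33.6 | 78% | 38.5 | 83% |
| 50% | 24.0 | 63% | 27.5 | 69% |
| 70% | 14.4 | 43% | 16.5 | 48% |

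For example, at 50%: 13.7 × √(2/24) = 3.955; 9.1 / 3.955 = 2.301; 2.301 − 1.960 = 0.341; Φ(0.341) = 0.633.

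**4. Naming baseline FACIT-FS.** Suppose 13.7 is the SD of the change, variances are equal at both times, and the comparator is an unadjusted change score. Adjustment then multiplies the variance by (1 + rho)/2.

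| rho | Variance factor | SD | n per arm for 90% | Power at 48 |
|---|---|---|---|---|
| 0.3 | 0.65 | 11.05 | 31 | 98% |
| 0.5 | 0.75 | 11.86 | 36 | 96% |
| 0.7 | 0.85 | 12.63 | 41 | 94% |

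**5. Naming the strata.** If tumour entity and site explain 2% to 10% of the variance (assumption), the SD becomes 13.7 × √(1 − R²). The requirement falls to 47 to 43 per arm, and power at 48 is 91% to 93%.

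**The case against.** The strongest reply is that the covariate list is introduced by way of example and the article condenses a fuller protocol. Strata and baseline may well be named there, and leaving them out of an open list is no error. That stands. A reader might infer that the plan throws away precision, but the documents do not support this. They specify mixed models on fatigue measured at baseline and weekly, not an unadjusted change score. Such a model can carry baseline as a response, and with a common baseline mean it recovers essentially the precision of covariate adjustment. Type of chemotherapy partly stands in for tumour entity. Omitting strata does not bias the estimate and tends to make the inference conservative.

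The open list does not settle the FIGO point. It leaves room to add terms, but it does not remove one that is named as going into the model.

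A second reply is that nobody would knowingly delete all breast patients, since the modified intention-to-treat set and the planned subgroup analyses by tumour type presuppose them, and FIGO may be loose shorthand for stage. This is fair, and it is why the consequence is something that can happen, not something that will. It also shows the gap: the stated set and the stated model agree only if a coding rule is supplied, and the article supplies none.

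Third, the power figures are a conditional worst case. That also stands. They assume a breast share and complete-case deletion, and starting from 55 per arm they are somewhat milder.

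**Conclusion.** The concern holds for FIGO stage. A term of the primary model is undefined for one eligible tumour group, and nothing in the article says how those patients are kept. Under complete-case handling they can be lost, in conflict with the modified intention-to-treat set. With an assumed breast share of 30% to 70%, power at 48 per arm would then be about 78% to 43% instead of 90%. This rests on three things: that FIGO does not stage breast cancer, which is general knowledge; the assumed share; and default deletion of incomplete records.

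A reader might infer that the primary analysis will be confined to non-breast patients. The article does not support that, because a 'not applicable' level avoids the loss completely.

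The unnamed strata and baseline score are an opportunity for improvement, not an established loss. The 94% to 98% power for rho 0.7 to 0.3 applies only against an unadjusted change score with 13.7 as the SD of change, and the Sample size section does not say whether 13.7 refers to the change or the score. The gain from the strata is small. Histological grade can stay where it is.

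**What to change.** 1. In the primary model, replace FIGO stage with a variable defined for every tumour type: either the treatment-setting term already in the list, or one common stage grouping. Alternatively, keep FIGO as a categorical term with a pre-stated 'not applicable' level. If tumour entity is also in the model, that level coincides with the breast category, and one of the two should be dropped as redundant.
2. State that no randomised patient in the modified intention-to-treat set is excluded because a covariate is missing or does not apply.
3. As a free improvement, name tumour entity, study site and baseline FACIT-FS in the primary model, with baseline either as a covariate or as a response with a common baseline mean, and close the list.
4. Use the same stage variable in the comparison of participants with non-participants.

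The cost is a few lines of text, fixed before outcome data are examined. Tumour entity and site are known at randomisation, baseline fatigue is already measured, and a common stage grouping can be derived from the oncologic history recorded at baseline. Sample size and visits do not change.

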#### Tumor response

Effects of IF on tumor response between intervention and control group will be compared by tumor specific markers (e.g. CA 125, CA 15-3, CEA, SCC, LDH), pathological response rates after neoadjuvant treatment as well as standardized radiologically evaluation with RECIST 1.1 criteria in metastasized cancers. Imaging will be obtained during routine clinical follow-up and will not be performed specifically for this trial. Radiological responses will be evaluated by a single radiologist blinded to the group allocation of the patient. Pathological responses will be extracted from official medical records after surgery. Pathologists will not be aware of trial participation or group allocation.

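### Pathological response is compared by an unstratified chi-square although randomisation is stratified by tumour entity; a test stratified by entity would be more sensitive and costs nothing

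*Protocol article*

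**What the plan says.** Under Statistical analysis, the protocol article fixes the comparison in one sentence: "Pathological response rates after neoadjuvant CHT will be compared using the Chi square test". No stratification factor or covariate is attached to it.

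The design does use tumour type. Under Recruitment and randomization: "Variable block randomization stratified by tumor entities and study site". Statistical analysis repeats this: "Patients will be randomized to the intervention or control group (1:1) stratified by tumor entity and study site". Table 2 under Eligibility criteria admits "Women with histologically confirmed ovarian (including peritoneal cancer or cancer of the fallopian tubes), breast, endometrial or cervical cancer".

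The confounder list under Statistical analysis belongs to the mixed models. It includes treatment setting ("neoadjuvant/adjuvant vs metastatic treatment") but does not name tumour entity. Treatment setting is not a randomisation stratum.

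Under Tumor response, pathological response stands beside tumour markers and radiological evaluation as one of three measures. Its source is the clinical record: "Pathological responses will be extracted from official medical records after surgery". It therefore exists only for neoadjuvant patients who reach surgery.

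The article also plans: "Subgroup analyses will be performed by tumor type and type of CHT regime for groups with an adequately high number of participants". It calls the secondary outcomes exploratory under both Statistical analysis and Limitations.

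**The concern.** Stratified blocks keep the arms close to 1:1 within each tumour entity, but the named test does not use that structure. If pathological response differs between entities, two things follow.

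- **Lost precision.** The unstratified test counts variation between entities as random error. Where the design has balanced entity across arms, that variation does not contribute to the difference between arms. The standard error is then too large and the test too cautious. This matters for an outcome that should reveal any loss of antitumour effect.
- **Sensitivity to tumour mix.** The subset analysed is defined by neoadjuvant treatment and surgery, which randomisation does not balance. The arms may by chance contain different proportions of each entity, and the pooled difference then moves with no treatment effect behind it.

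**Working it through.** **The plan's own figures.** The article gives no sample size, response rate or power for pathological response, so there is nothing to reproduce for this endpoint. The 48 per group under Sample size concerns fatigue (difference 9.1, SD 13.7, 90% power). It reproduces with the normal approximation but has no bearing here.

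**Inputs from the article.** 1:1 allocation, strata of tumour entity and site, 110 patients, two-sided 5% level.

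**Inputs assumed.** Number of neoadjuvant patients, tumour mix, response rates, block sizes and site split.

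**1. Why the unstratified test is conservative.** Take two equally frequent entities with response 60% and 10%, balanced across arms, and no effect.
- Variance used by the pooled test, per patient: 0.35 × 0.65 = 0.2275.
- Variance that actually drives the difference: (0.60 × 0.40 + 0.10 × 0.90)/2 = (0.24 + 0.09)/2 = 0.165.
- Ratio of true to assumed standard error: √(0.165/0.2275) = 0.85.
- The nominal cut-off of 1.96 therefore acts like 1.96/0.85 = 2.30, a two-sided level of about 2%.

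**2. Simulation with the tumour mix fixed** (30 neoadjuvant patients per arm, two entities). CMH is the Cochran-Mantel-Haenszel test stratified by entity.

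| Scenario | Mix, fasting vs control | Pooled rejects | CMH rejects |
|---|---|---|---|
| No effect, 60% and 10% | 15/15 vs 15/15 | 1.9% | 4.7% |
| No effect, 60% and 10% | 18/12 vs 12/18 | 8.6% | 4.9% |
| No effect, 50% and 30% | 18/12 vs 12/18 | 5.5% | 4.9% |
| True harm, 60% to 25% and 10% to 5% | 15/15 vs 15/15 | 43% | 50% |
| True harm, as above | 18/12 vs 12/18 | 19% | 49% |

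In the last row the imbalance favours the fasting arm and so masks the harm.

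**3. Simulation with random tumour mix.** 110 patients, blocks of 4 or 6 within entity and site, sites 60:40, on average 44 to 68 neoadjuvant patients. Response in the leading entity versus the others was 40% vs 10%, 60% vs 10% or 50% vs 30%. There was no effect, and 6,000 trials were run per scenario.
- Overall rejection: pooled 3.3% to 5.1%, CMH 4.4% to 5.5%.
- Difference between arms in the share of the leading entity: median 5 to 8 points, 90th percentile 13 to 19 points, 20 points or more in 1% to 8% of trials.
- In trials with an imbalance of 20 points or more: pooled rejects in about 3.5% to 17%, CMH in about 2% to 7.5%. These figures are imprecise because few trials qualify.

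**4. Shift caused by a given imbalance.** Spurious difference = imbalance in share × gap in response rates.
- 10 points × 30 points = 3 points.
- 20 × 20 = 4 points.
- 20 × 30 = 6 points.
- 20 × 50 = 10 points.

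**The case against.** The strongest reply is that the planned test is valid. A 5% test after randomisation already allows for chance imbalance, and the simulation supports this: the pooled test stays at or below about 5% overall. A reader might infer that chance tumour mix makes the plan prone to a false fasting benefit, but the documents and the arithmetic do not support that. Even a marked 25-point imbalance, 15/5 versus 10/10 with assumed response of 45% and 10%, gives (15 × 0.45 + 5 × 0.10)/20 = 36.25% against (10 × 0.45 + 10 × 0.10)/20 = 27.5%. Then z = 0.0875/√(0.31875 × 0.68125 × 2/20) ≈ 0.59 and p ≈ 0.55, so the planned test would report no difference. This objection stands in full. What remains is lost precision, and distortion only in the uncommon trial with a marked imbalance.

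Second, the endpoint is exploratory, the article acknowledges heterogeneity across cancer types, and it plans tumour-type subgroups. This makes the point minor but does not remove it. Subgroups are planned only where numbers are adequate, and separate small comparisons do not give one adjusted estimate.

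Third, the approved full protocol is not shown and may specify more; that the test pools entities is read from the absence of any stratification. That is a fair caution. Still, the article names a specific test, so this is a stated choice and not merely an omitted detail.

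**Conclusion.** The point holds as a free improvement to an exploratory analysis. The named test ignores a factor that the trial randomises by. Where response differs strongly by entity, this costs sensitivity: about 7 points of power (43% against 50%) in the assumed harm scenario with a balanced mix, and more if the imbalance happens to mask the harm. Where response rates are closer, the gain is small. All sizes rest on assumed response rates, tumour mix and neoadjuvant numbers, and the direction matters more than the exact figures.

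Two further readings are not supported. Pathological response is not the trial's sole check on antitumour effect: Tumor response lists three measures, and the Discussion ties that safety aim to laboratory values. The argument also does not carry over to grade 3 or higher adverse events, because they are not confined to the neoadjuvant subset and nothing worked out here concerns them.

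**What to change.** Replace the sentence on pathological response under Statistical analysis with one stating that response after neoadjuvant chemotherapy is compared by a Cochran-Mantel-Haenszel test stratified by tumour entity, in an exact version if cells are sparse. Report the stratified risk difference with its 95% confidence interval, label the analysis exploratory, and describe pathological response as one of three tumour-response measures. Leave the adverse-event comparison as it is.

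The cost is one sentence. Tumour entity is already recorded for randomisation, so no new data, visits or patients are needed. The gain will be limited for rare entities, since a stratum with patients in only one arm, or with no variation in response, adds nothing to the test.
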